#### Other measures

Also assessed at 20 weeks are adverse life events measured using two instruments: firstly, Section 1 of the Harvard Trauma Questionnaire (HTQ) which includes 17 items describing traumatic events [52], validated in Pakistan [53]. In addition, day-to-day life events will be assessed using a life-events measure developed for women in Pakistan [36]. Both the HTQ and life-events measure contain additional questions about whether events have occurred since trial enrolment to enhance sensitivity.

#### Further data

At baseline we will also collect demographic data on each participant, including age, marital status, years of schooling, and occupation of the woman. Where applicable we will also collect data on number of children and their ages, and years of schooling and occupation of the woman’s husband. Research assistants also subjectively assess the socioeconomic status of the household using a locally developed rating scale.

#### Qualitative evaluation

Semistructured interviews will be conducted with a random subsample of intervention facilitators; LHWs; intervention participants with an equal number of completers and dropouts; control arm participants; senior staff with policy implementation responsibilities/connected to the research (i.e. receiving referrals of excluded study participants); research assistants; and family members of intervention participants with an equal number of intervention completers and dropouts. We anticipate up to six interviews with each category of respondent, with sampling determined by saturation. Interviews follow a semistructured topic guide that address topics relevant to each category of respondent (see Table 2).

**Table 2 Tab2:** Qualitative evaluation

Category of respondent	Topics to be explored
Intervention facilitators	Overall impressions of PM+ Group Experiences of PM+ Group training and supervision Rapport with participants and families of participants Views on the group delivery format Experiences of participants’ intervention adherence and strategies to keep participants motivated View on intervention scalability
LHWs	Overall impressions of PM+ Group Strategies to keep participants motivated to attend the groups and experiences of participants intervention adherence View on intervention scalability with LHW as entry point into primary healthcare
Intervention participants – completers	Overall impressions of PM+ Group Rapport with group facilitators Intervention adherence Burden of research interviews
Intervention participants – drop outs	Reasons for stopping attending PM+ Group If appropriate: Rapport with group facilitator Intervention acceptability Burden of research
Control arm participants	Experiences of research, including participants and family views of the research assistants and research procedures Views of the questions researchers asked
Senior staff with policy implementation roles/connected to the research	Overall understanding and impressions of PM+ Group Existing scope of work of primary health care system in Pakistan, with a focus on LHW role Views on possible routes for integration and scale-up of PM+ Group into Pakistan primary health care systems
Research assistants	Views of assessment training and supervision Experiences of conducting research assessments, including the appropriateness of individual instruments, problems relating to masking, and experiences of participant distress
Family members of participants	Overall understanding and impressions of PM+ Group Where appropriate: Views of the impact of PM+ Group upon the participant in the family Views of the research assistants and assessments

*LHW* Lady Health Worker

Qualitative interviews and data analysis will be conducted by a pair of researchers independent of the research and intervention teams to avoid biasing responses. Researchers will be trained in the key principles of qualitative interviewing and also provided with supervision throughout data collection. Due to local community suspicions it is not possible to audio-record interviews; therefore, all interviews will be recorded in a written verbatim transcript produced as the interview is conducted [54]. Analysis will be conducted manually following an established thematic approach [54, 55].

### Masking

Due to the nature of the intervention it is not possible to mask participants, LHWs, and intervention facilitators and co-facilitators to treatment allocation. All researchers conducting quantitative outcome assessments will be masked, while the qualitative research team will be unmasked. Researchers conducting assessments are residents of the local Swat District and remain distinct to the intervention facilitation and co-facilitator teams with separate offices, logistical arrangements, and administrative management. They are trained and supervised by the site principal investigator (PI; NK).

Prior to each assessment point participants are instructed by LHWs not to disclose to researchers their allocation status. The researcher completes a form to guess which arm of the trial the participant belongs to both preceding and following the conduct of each assessment. The order of assessments ensures that the primary outcome measure (HADS) is administered first to minimise the risk of bias should masking be compromised. If unmasking does occur this will be documented, the assessment halted, and a new researcher assigned to complete assessments with that participant. The CSRI is administered as the final instrument at the 20-week assessment to minimise the impact upon assessments should responses lead to unmasking.

The trial statistician (DW) is blinded to the treatment code when developing the statistical analysis plan and writing the statistical programmes, which will be validated and completed using dummy randomisation codes. The actual allocation will only be provided after locking of the database.

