### Sample size and power calculations

Similar community-based intervention studies using change in symptom-based questionnaires, like the Hospital Anxiety and Depression Scale (HADS) [35–37], have used effect sizes of at least 0.4 when testing treatment as usual groups with limited or no active therapeutic elements, as we propose. Assuming an effect size of 0.4 for the primary endpoint (HADS total score at 20 weeks), with 90% power and 5% significance, an intracluster correlation coefficient of 0.05, and a two-sided hypothesis test with 34 health worker catchment area clusters randomised at a 1:1 allocation ratio, and accounting for 20% attrition, we will need 612 participants (i.e. 306 in each arm). This means that we will need on average 18 participants from each of the 34 health worker catchment areas. A pilot study conducted a nearby Union Council found that these recruitment numbers were feasible and achievable [27], and previous research in the same setting identified a high prevalence of mental health problems in women [38].

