### Randomisation

Thirty-four LHW clusters will be randomised to the intervention and control arms on a 1:1 allocation ratio using a permuted-block randomisation method (see Fig. 2). A randomisation list will be generated by an independent statistician using SAS PROC PLAN. Allocation of clusters will be carried out by an independent person based at the Human Development Research Foundation, Islamabad. This is achieved by the research team sharing a list of LHWs each with a corresponding number. Allocation status will be communicated to the research team coordinator who will inform respective LHWs after consent for trial participation is obtained from participants by researchers.

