**Fig. 2 Fig2:**
[figure not shown]
Schedule of enrolment, interventions, and assessments

If a catchment area is allocated to the intervention arm, the LHW contacts all participants within her cluster to schedule an initial meeting to introduce the participant to the intervention facilitator. This is a necessary engagement step in this setting where service uptake is dependent upon a trusted relationship with the service provider. If allocated to the control arm the LHW continues routine visits to women in her catchment area.

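### The unmasking rule replaces the researcher for one participant only, although every woman in the LHW catchment area is in the same arm

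*Protocol article*

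**What the plan says.** The Masking section sets the standard: "All researchers conducting quantitative outcome assessments will be masked, while the qualitative research team will be unmasked". It then fixes what happens when masking fails: "If unmasking does occur this will be documented, the assessment halted, and a new researcher assigned to complete assessments with that participant". Two features of the interview are meant to limit the damage. The CSRI comes last at 20 weeks, and the primary outcome comes first: "The order of assessments ensures that the primary outcome measure (HADS) is administered first to minimise the risk of bias should masking be compromised". Researchers also record a guess of the participant's arm before and after every assessment, and LHWs ask participants beforehand not to reveal it.

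The unit of allocation is given under Randomisation: "Thirty-four LHW clusters will be randomised to the intervention and control arms on a 1:1 allocation ratio". The text after Fig. 2 confirms that a whole area takes one arm: "If a catchment area is allocated to the intervention arm, the LHW contacts all participants within her cluster". The sample size section gives the cluster size: "we will need on average 18 participants from each of the 34 health worker catchment areas". Outcomes are assessed after randomisation at 7 and 20 weeks.

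**The concern.** The rule would suit an individually randomised trial, where one woman's disclosure says little about the next woman's arm. Here it reveals the arm of everyone under the same LHW. The rule changes the researcher for the woman who disclosed and is silent on the rest of the cluster.

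The order of instruments does not close this gap. HADS first and CSRI last limit bias within the interview in which the disclosure occurs. For the next woman in that area, the researcher already knows the arm when the HADS starts. The CSRI can itself reveal the arm at the end of one visit, and that knowledge goes with her to the next.

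The primary outcome is a symptom scale administered by researchers to participants who cannot be masked. The single-blind design therefore rests on the assessors, and the rule as written allows part of that protection to be lost.

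**Working it through.** **The plan's own figures.** With an effect size of 0.4, 90% power and two-sided 5% significance:

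- Per arm before clustering: 2 × (1.960 + 1.282)² / 0.4² = 131.4, rounded up to 132.
- Design effect with 18 per cluster and ICC 0.05: 1 + 17 × 0.05 = 1.85, so 132 × 1.85 = 244.2.
- With 20% attrition: 244.2 / 0.8 = 305.25, rounded up to 306 per arm, or 612 in all.
- 612 / 34 = 18 per cluster.

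The sample size reproduces and is not in question. Only the cluster size is used below.

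**Scope of the rule against scope of the knowledge.**

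| | Women covered |
|---|---|
| Arm revealed by one disclosure | the whole catchment area, 18 on average |
| Researcher replaced under the rule | 1 |
| Other women whose arm she now knows | 18 − 1 = 17 (about 13 if 20% are lost: 14.4 − 1) |

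Women she assessed earlier in the same round are unaffected for that round. The exposed assessments are those she makes in that area afterwards.

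**Illustrative size at one visit.** Inputs from the article: 18 women per cluster and 20% attrition, giving m = 18 × 0.8 = 14.4. Assumptions, not in the article: each woman discloses independently with probability p; one researcher assesses the whole cluster; she knows which catchment area each woman belongs to.

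The woman seen in position j is assessed after unmasking if any of the j − 1 women before her disclosed, which has probability 1 − (1 − p)^(j − 1). Averaged over positions, the share is

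1 − [1 − (1 − p)^m] / (m × p).

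| p | Clusters with any disclosure, 1 − (1 − p)^14.4 | m × p | Share of HADS taken after unmasking |
|---|---|---|---|
| 2% | 0.252 | 0.288 | 1 − 0.252/0.288 = 12% |
| 5% | 0.522 | 0.720 | 1 − 0.522/0.720 = 27% |
| 10% | 0.781 | 1.440 | 1 − 0.781/1.440 = 46% |

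**If three researchers share the cluster equally** (also an assumption), m = 14.4 / 3 = 4.8 for each, and the same formula gives 4%, 9% and 17%.

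**If one researcher covers the cluster at both visits** (a further assumption), what she learned at 7 weeks carries over. The share of 20-week HADS taken after unmasking is 1 − (1 − p)^14.4 × [1 − (1 − p)^14.4] / (14.4 × p), which is 34%, 65% and 88%. The article does not say whether researchers return to the same area, so this shows only how strongly the answer depends on the rota.

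**The case against.** The best defence is that the same section requires all outcome assessors to be masked, so sending a researcher known to be unmasked back into the area would breach that requirement. On this view, rota details belong in a field manual or the full protocol, which is not shown. Part of this stands: the article does not say how researchers are assigned, whether they return at 20 weeks, or whether they know a woman's catchment area. The last is likely, because households are listed and approached through the LHW, but it is not stated. What does not stand is treating the point as omitted detail. The article states a remedy and limits it to one participant, and that limit does not match the unit of allocation.

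Three stronger readings are tempting and are not supported.

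- A reader might infer that later assessments by this researcher would be recorded as masked. The article does not say so. The guess made before each assessment may capture what she already knows. A guess is not a documented unmasking, however, and nothing follows from it.
- A reader might take the proportion of clusters with any disclosure (25%, 52% or 78%) as the size of the problem. That counts clusters. The affected HADS assessments are about half that share or less, even when one researcher covers the cluster.
- A reader might conclude that the HADS comparison is biased by a known amount. The documents give nothing from which to estimate that. HADS answers come from women who know their arm, so part of the risk remains whatever the researcher knows.

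The section's other safeguards (separate teams and offices, the LHWs' instruction, halting the interview) do lower the chance of disclosure or limit its effect within one interview. They do not act on the rest of the cluster.

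**Conclusion.** The point holds as a mismatch between a stated rule and the design. Knowledge of allocation is shared across a cluster, while the remedy covers one woman, leaving about 17 others whose arm the researcher knows and whom nothing stated prevents her from assessing.

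The practical size is uncertain. On assumed disclosure rates of 2%, 5% and 10%, about 12%, 27% or 46% of HADS assessments at a visit would follow unmasking if one researcher covers a cluster of 14.4, and fewer if the cluster is shared. These figures describe exposure; they do not estimate bias in the treatment effect. The change is worth making because it is cheap and protects the primary outcome, but the article does not show that masking will fail on any particular scale.

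**What to change.** Extend the replacement rule from the participant to the catchment area:

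1. After any unmasking, give the remaining 7- and 20-week assessments in that area, where the existing team allows, to a researcher still masked to it.
2. Log each unmasking by cluster and assessor.
3. Flag as unmasked any later assessment that the same researcher nevertheless makes there.

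A HADS analysis without the flagged assessments may be added as supportive only. Exclusion depends on an event after randomisation that may be more common in one arm, so the analysis can introduce selection bias of its own and should not replace the intention-to-treat result.

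The cost is swapping visits within the team and extra fields in the log. The article gives no team size, so it cannot be promised that a swap will always be possible; the flag covers the cases where it is not. Sample size, treatment and primary analysis stay as they are. Recruitment was still under way at submission, so follow-up visits not yet made at that time could have benefited.

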### Data management

Quantitative data will be completed on paper assessment booklets with assigned participant codes, stored at the research field office at the end of each day. Daily checking of data will be performed by the research coordinator, with queries identified and resolved promptly. Double data entry will be conducted by an assigned data entry team at the Human Development Research Foundation (HDRF) in Islamabad, with discrepancies resolved by a third data entry person. Once in an electronic file, all data will be password-protected, with data managers controlling access to the passwords and the database backed up daily.

Qualitative data will be stored in paper format in locked filing cabinets in the research field office at the end of each day. None of the qualitative data will contain identifiers (name, age, category of respondent, etc.) that may compromise participant anonymity.

All other process data (i.e. supervision forms) will be stored in locked filing cabinets in the intervention field office. Intervention team members have been trained in the importance of de-identifying all notes relating to participant progress through the intervention to ensure confidentiality.

### Statistical methods

Data will be analysed using SAS 9.3 and SPSS Version 21. Findings will be reported according to the Consolidated Standards of Reporting Trials (CONSORT) guidelines for cRCTs [56]. Primary analyses will be based on the intention-to-treat population and secondary analyses will be based on the per-protocol population. A linear mixed model will be employed for the primary endpoint analysis. The mixed model will have treatment, visit, interaction between treatment and visit as fixed effects, baseline measurement of HADS as covariate, and cluster and subject as random effects. The mean difference between two treatment arms at each visit, together with its 95% confidence interval (CI), will be derived from the mixed model. Covariate-adjusted mixed model of primary endpoint will also be performed by adding prespecified covariates at baseline into the above model. Missing data will be treated as missing at random in the mixed model analysis and no imputation of primary endpoint will be made. To assess the sensitivity of the result to this assumption, the last observation carried forward strategy will be used to compute missing primary endpoints. Subgroup analysis will be performed on the prespecified covariates.

Continuous secondary outcomes will be analysed in a similar way as the primary endpoint analysis. For the analysis of binary secondary outcomes, a generalised mixed model will be employed with treatment, visit, interaction between treatment and visit as fixed effects, baseline measurement as covariate, and cluster and subject as random effect. The odds ratio between two treatment arms at each visit together with its 95% CI will be derived from the generalised mixed model.

All analyses will be described in detail in the finalised and signed statistical analysis plan before unmasking the study.

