### Design and setting

This is a two-arm, single-blind, cluster randomised controlled superiority trial conducted in a community-based setting with women in rural Pakistan. A cRCT was favoured to reduce the likelihood of contamination between the two groups. The Standard Protocol Items: Recommendations for Interventional Trials (SPIRIT) figure 2013 is provided in Fig. 1, and the SPIRIT Checklist accompanies this paper as Additional file 1.

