### PM+ Group intervention

PM+ is a brief WHO psychological intervention based on evidence of established behavioural techniques for addressing symptoms of common mental health problems in low- and middle-income countries. The manualised intervention involves empirically supported strategies of problem-solving, behavioural activation, accessing social support, and stress management training [23, 26]. Prior to implementation, a period of formative work was undertaken to contextually adapt the intervention and training materials for delivery to women in Swat, Pakistan, and a pilot trial conducted [27].

PM+ Group is an adaptation of the individual PM+ intervention. It was developed through 6 months of formative work, including review by 28 international experts. The group intervention (manual available upon request) involves five weekly sessions each lasting for 3 h, inclusive of breaks. The first session opens with psychoeducation, including information on common reactions to adversity, the rationale for PM+, goal setting, and brief motivational interviewing. Sessions 1 to 4 each introduce a strategy: (1) Managing Stress, (2) Managing Problems, (3) Get Going, Keep Doing (i.e., behavioural activation), and (4) Strengthening Social Support that are applied by participants to problems that they are facing. Each strategy is reviewed in subsequent sessions, with application of strategies between sessions encouraged to enhance learning through repetition. The final session involves a revision of learning, education on preventing relapse, and ends with a culturally appropriate closing ceremony. To enhance accessibility for illiterate individuals the programme is structured around locally relevant and appropriate pictorial materials and adopts a narrative format to support engagement and individual disclosure of personal difficulties which can be more difficult in a group format. Specifically, a case example of a woman experiencing common practical and emotional problems is shared each week, with participants following her progress through PM+ Group.

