### Enhanced usual care (EUC)

Control and intervention arm participants will continue to receive routine LHW visits on an individual basis. The care that they receive is considered to be EUC as usual care for common mental disorders in primary care in Pakistan typically involves no or placebo care leaving the majority of cases of distress undetected and unsupported. EUC will comprise:Providing LHWs and primary health care providers with training in the detection and management of mental health care needs, and referral pathwaysProviding feedback to all participants about their assessment resultsProviding all participants with information about the options for seeking appropriate care for distress (i.e. through their LHW, the BHU, or the tertiary health care centre)

Both arms have unrestricted access to EUC through their routine health providers. The intensity of services received in both arms will be measured at 20 weeks as part of the economic evaluation (see below).

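### The analysis-population sentence can be read as putting the secondary outcomes on the per-protocol set alone, and any attendance-based version of that set would restrict only the PM+ arm

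*Protocol article*

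**What the plan says.** The rule on populations is one sentence in Statistical methods: "Primary analyses will be based on the intention-to-treat population and secondary analyses will be based on the per-protocol population". Neither population is defined there, and the sentence does not say whether *secondary analyses* means analyses of the secondary outcomes or supportive re-analyses of the primary endpoint. The next paragraph of the same section says "Continuous secondary outcomes will be analysed in a similar way as the primary endpoint analysis". It then sets out a generalised mixed model for binary secondary outcomes, again without naming a population. The section closes by deferring detail to a signed statistical analysis plan, which is not shown.

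On the design:
- Design and setting calls the study a "cluster randomised controlled superiority trial".
- The PM+ Group intervention "involves five weekly sessions each lasting for 3 h, inclusive of breaks".
- Under Enhanced usual care, "Control and intervention arm participants will continue to receive routine LHW visits on an individual basis", and "Both arms have unrestricted access to EUC through their routine health providers".
- The Randomisation section adds: "If allocated to the control arm the LHW continues routine visits to women in her catchment area".
- The Qualitative evaluation section samples "intervention participants with an equal number of completers and dropouts; control arm participants". Among trial participants it divides only the PM+ women into completers and dropouts.

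**The concern.** In a superiority trial the randomised comparison is protected by analysing everyone as allocated. A plan that names per-protocol as the population for its secondary analyses, and names no other, lets the secondary outcomes be reported on a non-randomised set alone.

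In this design the filter could also be lopsided. PM+ women have five sessions that they may or may not attend; control women have nothing comparable to comply with. If per-protocol were defined by attendance, women would be removed from one arm only.

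The article gives reasons why attendance may not be random with respect to outcome. It describes conservative norms that limit women's access to services, a need for family permission to take part in research, and uptake that depends on trust in the provider. The planned baseline covariate would reduce imbalance in the starting score but would not remove selection on factors of this kind.

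At stake are the conclusions on functioning, depression, PTSD symptoms and social support. An ambiguous rule also leaves room to choose the reading after results are known, unless the analysis plan closes it.

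**Working it through.** **1. The plan's own figure.** The sample size is not in dispute. From the Sample size section: effect 0.4 SD, two-sided 5%, 90% power, ICC 0.05, 18 women per cluster, 34 clusters, 20% attrition.
- Individual randomisation: 2 × ((1.960 + 1.282)/0.4)² = 131.3 per arm.
- Design effect: 1 + (18 − 1) × 0.05 = 1.85, giving 131.3 × 1.85 = 243 per arm.
- Attrition: 243/0.80 = 304 per arm, 608 in total, or about 17.9 per cluster.
- Rounded up to 18 in each of 17 clusters per arm: 306 per arm, 612 in total, as stated.

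**2. What the sentences determine.**
- Primary endpoint: intention to treat under either reading.
- Continuous secondary outcomes: the population sentence can be read as per-protocol. The later sentence can be read as carrying over the primary analysis in full, population included, or only its model.
- Binary secondary outcomes: the model is spelled out and no population is given, so the population sentence is all there is.

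**3. What an attendance filter would do.** Let q be the share of PM+ women removed and g the gap in SD by which they would do worse than attenders in either arm. With no treatment effect, and attenders' mean as zero, both full arms have mean q × g (higher is worse). Removing non-attenders from PM+ alone moves that arm's mean to 0. The spurious difference is therefore q × g. The document gives neither q nor g, so both are assumptions.
- q = 0.30, g = 0.25: 0.075 SD, and 0.075/0.4 = 19% of the design effect.
- q = 0.20, g = 0.10: 0.02 SD (5%).
- q = 0.40, g = 0.40: 0.16 SD (40%).
- g = 0: no bias.
- g negative (women who stop because they have improved): the same sizes with the sign reversed, against PM+.

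**4. A second parameterisation, also on assumed inputs.** Let p be the share of followed-up PM+ women who attend and ρ the correlation between propensity to attend and a better baseline-adjusted outcome. The spurious difference is ρ × φ(Φ⁻¹(1 − p))/p. For the false-positive rate, take 17 clusters per arm, ICC 0.05, 18 × 0.8 = 14.4 followed-up women per control cluster and 14.4 × p per PM+ cluster, with a normal approximation.

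| p | Difference, ρ = 0.1 to 0.3 | Two-sided false-positive rate |
|---|---|---|
| 0.9 | 0.02-0.06 SD | 5.3-7.8% |
| 0.7 | 0.05-0.15 SD | 6.9-22.6% |
| 0.5 | 0.08-0.24 SD | 9.3-44.0% |

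As a check at p = 0.7: the variance is 1.67/244.8 + 1.454/171.4 = 0.0153, so SE = 0.124 SD. With ρ = 0.3, the difference is 0.3 × 0.348/0.7 = 0.149 SD, or 1.20 SE, which gives 22.6%. With ρ = 0 the rate stays at 5%.

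**The case against.** The strongest reply is that the article never equates *secondary analyses* with *secondary outcomes*. It uses the second term when it means outcomes, and it says those that are continuous are handled like the primary endpoint, whose analysis is by intention to treat. On that reading per-protocol is a supportive re-analysis alongside the main one, which is common practice. This has real force: it makes the sentence ambiguous rather than plainly wrong. It does not close the question, because the later sentence follows a description of a model, names no population and covers continuous outcomes only.

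A reader might go further and infer that the secondary analyses will compare selected attenders with all controls. The document does not support that. It does not define per-protocol by attendance and does not say that every control is kept. The set could rest on eligibility violations or other deviations, which can occur in both arms. Its definition belongs in the analysis plan, so its absence here is no fault.

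A reader might also infer that the bias must favour PM+. That would need non-attenders to have the worse prognosis. No attendance rate, reason for stopping or link to outcome is reported; reasons for stopping are listed as something to explore in interviews.

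**Conclusion.** The point holds as a correction to a stated rule. The population sentence can be read as making per-protocol the only basis for the secondary outcomes, and nothing else in the article rules this out. If the set were defined by attendance, it would restrict the PM+ arm alone and the comparison would no longer be randomised.

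The direction is open and the size cannot be derived from the document. The 0.02-0.16 SD illustration rests wholly on the assumed non-attendance and prognostic gap. The false-positive rates rest further on an assumed selection correlation and on using the HADS planning ICC and attrition for a secondary outcome. The primary conclusion and the sample size of 612 are untouched.

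**What to change.** Replace the population sentence with a statement that all primary and secondary outcomes, continuous and binary, are analysed by intention to treat. State that any per-protocol analysis is supportive only, that its set is defined before unmasking and, if it depends on attendance, that it is reported as a non-randomised comparison restricting the PM+ arm. The cost is a change of wording here and in the analysis plan; no new data are needed and the sample size is unchanged.

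Optionally, if an effect in attenders is wanted, add a complier-average causal effect analysis with allocation as the instrument, allowance for clustering and a session threshold fixed before unmasking. Two cautions apply. The article does not say that session attendance is recorded, so this must be confirmed first. The method also assumes no effect below the threshold, which is doubtful when the first session already provides psychoeducation and a strategy. Its interval will be wider than the intention-to-treat interval. This is a choice for the trial team; the correction does not depend on it.
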